### Participants

The Eira unit can manage 30 patients simultaneously, and all patients included in the CM intervention will be asked to participate in the study. Eira accepts patients who have been suffering from ED for at least 10 years and participated in at least three failed treatment efforts in specialized ED units. Since they have been ill for a long time and since previous treatment efforts have been unsuccessful, patients participating in the study will act as their own controls.

The study is approved by the ethical review board in Stockholm in compliance with the Helsinki Declaration.

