### Outcome

Primary outcome is quality of life. Secondary outcomes are health care consumption and costs, and ED symptoms at 1, 2 and 3 years follow-up.

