## Discussion

The treatment of patients with SEED often causes frustration and confusion among ED clinicians, since these patients often have tried “everything” without a lasting positive effect. In our clinical experience this often results in a situation where patients are considered “unmotivated” and dismissed from treatment, which in turn often leads to a symptom deterioration and that patients eventually return to the clinic in need for more acute interventions. As an alternative, clinicians may continue to offer patients interventions that neither therapist nor patient believes is helpful – at least not in a longer perspective. It might be time to re-evaluate what a positive outcome is for these patients.

CM provides an alternative to traditional treatment aiming at symptom reduction. CM aims to improve the patients’ quality of life, enhance their social functioning, and promote their ability to live as independently as possible despite their illness. CM offers unconditional long-term support, without requiring treatment progress. Instead CM stresses stabilization and harm-minimizing interventions, which are assumed to both increase quality of life and social functioning and to reduce the number and length of hospitalizations.

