There has been no similar service for patients with ED in Sweden or, to our knowledge, anywhere else. For a long time, CM has been used for patients with serious mental disabilities, such as schizophrenia, other psychoses or personality disorders, as well as for serious substance abuse problems. Since previous studies have shown similarities between SEED patients and patients with schizophrenia [2], it is reasonable to think that CM can be helpful also for SEED. However, we stress that CM is not an intervention for patients with a short duration of illness. For these patients, full recovery should be the main focus. It is also important to point out that CM is not to be seen as a “last resort” or as palliative care. The patients’ goals, life situation and abilities must always be the guiding principle in any intervention, and an important task for the case manager is to always keep an open dialogue with the patients. Although the patients previously have not had a lasting effect of any treatment interventions, this is never to be seen as a “failure”. At another time, in another life situation, the conditions may be better. One of the case managers’ tasks is to guide and help the patients to get access to the right intervention at the right time, and to create the best possible conditions for this intervention.

The primary outcome of this study is quality of life, which will be measured with both quantitative and qualitative measures. It is important to learn more about how SEED patients define quality of life. Is it to have fewer ED symptoms? Better economy? Or is it to be at peace with the ED, without the risk of becoming somatically too ill? Secondary outcome measures are ED diagnosis, ED symptoms, treatment satisfaction and health care consumption. In terms of ED diagnosis, there is no goal of remission with the support of CM. However, it is important to monitor any changes in ED diagnosis and symptoms over time.

The patients’ acceptance of CM at Eira will also be followed up with both quantitative and qualitative measures, to gain an understanding of the patients’ thoughts about the intervention. Perhaps CM will impact the SEED patients’ positively, but there is also a risk that patients will feel more vulnerable and alone when active treatment to reduce symptoms or pushing for weight gain is terminated.

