The entire study is uncontrolled and compares conditions before and during the intervention based on an assumption that no changes would occur without the intervention. This assumption creates uncertainty and the sensitivity analysis is therefore particularly important. Especially sensitive to external influences are healthcare usage and productions costs will be considered. They can be affected by changes in the health care organization, enrolment principles and changes in the labour market. Therefore, these conditions will be specifically studied, and in the sensitivity analysis cost-effectiveness will also be estimated without those possible benefits.

In summary, it is our hope that CM, despite its seemingly limited ambitions, will prove to improve living conditions for SEED patients as well as to reduce society’s cost.

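### The one sensitivity scenario described varies costs only, so the QALY gain and the primary quality-of-life change keep an untested no-change counterfactual

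*Protocol article*

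**What the plan says.** Under Participants, the protocol article makes patients their own controls, with this reason: "Since they have been ill for a long time and since previous treatment efforts have been unsuccessful". The Discussion states the consequence, that the study "compares conditions before and during the intervention based on an assumption that no changes would occur without the intervention", and draws the lesson: "This assumption creates uncertainty and the sensitivity analysis is therefore particularly important".

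The same paragraph then turns to costs ("Especially sensitive to external influences are healthcare usage and productions costs will be considered"), lists outside influences on them, and gives one concrete scenario: "in the sensitivity analysis cost-effectiveness will also be estimated without those possible benefits". The benefits meant are those in health care use and production.

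The outcome side is set out elsewhere. The Outcome section says: "Primary outcome is quality of life". Measures and Table 1 place RAND-36 at baseline and at 1, 2 and 3 years, so there is one value before treatment. Evaluation of cost-effectiveness takes QALYs from the same RAND-36 answers, converted to SF-6D, and adds an acceptability analysis over different willingness to pay. Specific aims asks, in causal terms, what entry to the programme leads to.

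**The concern.** The article declares the no-change assumption for the entire study, but the check it describes reaches only one side of the cost-utility analysis. The other side, the health effect, comes from the same instrument as the primary outcome. One untested assumption therefore supports both the primary result and the QALY gain.

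This is also where the data say least about what would have happened otherwise. Care use can be traced back through medical records, which the article says are collected retrospectively. RAND-36 has a single pre-treatment point, so no earlier trend in quality of life can be seen.

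If scores would have moved without CM, the primary change, the QALY gain, the cost per QALY and the acceptability curve would all be off by that movement. The described scenario would give no warning of it.

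**Working it through.** The article gives no sample size, standard deviation, effect size or power, so there is no figure of its own to reproduce. The arithmetic below shows only how a change that is not due to CM passes through the described analyses.

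**Inputs from the article**
- RAND-36, and hence SF-6D utility, at 0, 1, 2 and 3 years (Table 1).
- Time horizon of 3 years (Evaluation of cost-effectiveness).
- Assumed change without CM: zero (Discussion).

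**Assumptions made here**
- Utility is interpolated linearly between visits, without discounting.
- CM itself has no effect on utility.
- The utility change d that would have occurred anyway is 0.02 to 0.05. The article gives no such figure.

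**Step 1: QALYs wrongly credited.** The gain is the area between the observed utility path and baseline carried forward.
- Change d reached by year 1 and sustained: (0 + d)/2 + (d + d)/2 + (d + d)/2 = 0.5d + d + d = 2.5d.
- Change building linearly to d at year 3: d/6 + d/2 + 5d/6 = 1.5d.

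| Assumed d | Sustained from year 1 (2.5d) | Linear to year 3 (1.5d) |
|---|---|---|
| 0.02 | 0.05 QALY | 0.03 QALY |
| 0.03 | 0.075 QALY | 0.045 QALY |
| 0.05 | 0.125 QALY | 0.075 QALY |

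For a fall of the same size without CM, the signs reverse: a real CM gain would be understated by these amounts.

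**Step 2: what the described scenario changes.** Let G be the observed QALY gain, K the cost of CM, and H and P the savings in health care and production.
- Main analysis: (K − H − P)/G.
- Described scenario: K/G.
- With a sustained non-CM change d: the denominator should be G − 2.5d.

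The described scenario alters the numerator only. G, and any part of it not due to CM, is the same in both analyses.

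**Step 3: the acceptability analysis.** This varies the value placed on a QALY. It takes the counterfactual as given and so does not test it.

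**Step 4: break-even.** For a sustained change, the gain vanishes at d = G/2.5. An observed gain of 0.125 QALY, for example, would be fully explained by 0.125/2.5 = 0.05 utility. For mean RAND-36 at a given visit, the break-even is the observed change itself.

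**The case against.** The strongest reply is that this is a condensed article. It admits the limitation openly, and its wording (especially, also) marks the cost scenario as an addition and not as a full list. Further scenarios may stand in a document not shown. This is fair: a reader might infer that no other sensitivity analysis is planned, and the article does not say so. What remains is that, where the article gives its remedy for an assumption covering the entire study, the remedy it describes leaves out the primary outcome.

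Three stronger readings are tempting and are not supported.

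- **That the article contradicts its own no-change assumption.** The remark that "patients eventually return to the clinic in need for more acute interventions" concerns patients dismissed from treatment and describes worsening. Untreated worsening would make a flat counterfactual conservative. The remark "At another time, in another life situation, the conditions may be better" sits among sentences about earlier treatments without lasting effect and access to the right intervention at the right time. It concerns readiness for a later treatment, not improvement without one. Neither speaks of RAND-36 scores.
- **That baseline is likely to be a low point.** Entry requires at least 10 years of illness and at least three failed specialist treatments. These select for chronicity; no crisis or quality-of-life threshold is stated. Entry at a trough is possible but not documented.
- **That dropping cost changes could flatter the programme if costs rise.** The text removes possible benefits, and does so alongside the main analysis. A rise in cost is not a benefit and would still show there.

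The qualitative interview, held by a psychologist outside the unit's staff, asks whether quality of life has been affected. It is useful context but not a test of the counterfactual.

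**Conclusion.** The point holds as a gap in the scope of the described check. The Discussion ties sensitivity analysis to an assumption that governs the whole study, then describes varying costs only. In every analysis described, the QALY gain and the primary quality-of-life change absorb whatever would have happened without CM.

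The size is conditional: 2.5 QALY per unit of sustained non-CM utility change over 3 years, or 0.05 to 0.125 QALY for assumed changes of 0.02 to 0.05, and 1.5 per unit if the change builds linearly. The multipliers follow from the visit schedule and linear interpolation; the values of d are assumptions. The direction is open, so the finding is not that the gain will be overstated. No false-positive rate is given, because the article states no sample size or standard deviation, and the 30 patients mentioned are the unit's capacity at one time.

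**What to change.** Extend the sensitivity analysis in the Discussion to the health effect:

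- Replace the flat baseline with a range of non-CM utility changes in both directions (rebound and decline), fixed before the follow-up data are examined. Re-run the QALY gain, cost per QALY and acceptability curve for each.
- Report the break-even non-CM change at which the QALY gain becomes zero, and the same for the RAND-36 change. Giving it for the confidence limit nearer zero as well as for the point estimate would make the RAND-36 version more informative.
- Keep the existing cost scenario as it is.
- Word the conclusion as change during CM, and adjust the causal form of the question in Specific aims to match.

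The cost is a few extra model runs and some rewording, with no new data. The downside is a less definite conclusion, which is what one pre-treatment measurement and no control group can support.

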## Abbreviations

BMI: Body Mass Index is defined as Weight in kilos/(Length in meters) ^2^
CM: Case management
ED: Eating disorder
SEED: Severe and enduring eating disorder
